## Abstract

**Background:**

Kinesiotherapy is an option to mitigate worsening neuropsychomotor function due to human aging. Moreover, exergames are beneficial for the practice of physical therapy by older patients. Physical exercise interventions are known to alter the epigenome, but little is known about their association with exergames.

**Objective:**

We aim to evaluate the effects of kinesiotherapy with exergaming on older women’s epigenetic marks and cognitive ability, as well as on their clinical functional variables. Our hypothesis states that this kind of therapy can elicit equal or even better outcomes than conventional therapy.

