### Aims and Hypothesis

There is emerging evidence that physical exercise interventions can alter the epigenome, and the outcomes could be related to specific pathways [29,30]. However, to the best of our knowledge, there is still no evidence in the literature addressing the association of exergaming with epigenetic marks. Given the heterogeneity and complexity of the existing literature, more research is required in this emerging area to identify epigenetic marks that could serve as indicators of exercise adaptations [29]. In this perspective, this study aims to evaluate the effects of kinesiotherapy with exergaming on older women’s epigenetic marks and cognitive ability, alongside the evolvement of clinical functional variables. We hypothesize that this kind of therapy can elicit satisfactory results, with similar or even better outcomes than those of conventional therapies.

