### Sample, Eligibility, and Allocation

We will recruit 24 participants, exclusively women aged 60 years and over, at the School Clinic of Studies and Professional Practices of the Regional Integrated University of Upper Uruguay and Missions, which is located in Erechim, Rio Grande do Sul, Brazil. The sample size was based on the studies that used a similar methodology to assess the effect of exercise on epigenetic marks and the effect of improved functional mobility induced by running in the older women, related to epigenetic marks [8,9], considering the global H4 histone acetylation levels variable from earlier studies [33,34]. Sample size was calculated using G*Power software [35] considering an effect size of 1.3, two tails, an error probability of .05, and a power of 0.8.

After the invitation to take part in the study, the participants will sign a consent form and complete a demographic questionnaire. The following inclusion criteria will be verified: age 60 years or older; ability to ambulate effectively; absence of any reported diagnosis of neurological, cardiac, or any other disease that restricts physical exercise; absence of depression confirmed by the Geriatric Depression Scale—Short Form [36]; cognitive ability confirmed by the Mini-Mental State Examination, Brazilian version [37]; and acceptance of the commitment not to undergo any other physical therapy during the study.

The sample will have stratified randomization for 2 groups with 12 participants each. Patients will be selected by order of agreement to participate in the study until the number of patients stipulated for either of the groups is reached. The intervention group will practice kinesiotherapy exercises with the exergame, whereas the control group will practice conventional kinesiotherapy exercises without exergaming. Owing to the nature of the intervention, masking of the physical therapists and participants is not possible. However, data will be collected and analyzed by professionals masked to the allocation of the groups.

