We expect that both groups have improvements in muscle strength, balance, and cognitive ability, as both of them will exercise. However, due to the motivational and enriching aspects of the exergame, we expect the intervention group to show a significant improvement compared to the control group. We assume that improvement in functional clinical outcomes in the exergame group will be associated with increased BDNF levels and global acetylation of histones H3 and H4. Strategies that modulate BDNF and acetylation levels might be indicated to improve memory in the older population. Many studies have already shown that exercise is a strong epigenetic modulator that increases BDNF levels [7-9,33,62].

Research on this topic is likely to significantly expand the understanding of kinesiotherapy and the impact of exergames for older women. To the best of our knowledge, this may be one of the first studies exploring epigenetic outcomes of exergaming interventions.

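### The hypothesis claims equal-or-better outcomes, but the trial is sized to detect a difference and sets no margin or interval rule for equality

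*Protocol article*

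**What the plan says.** The hypothesis appears twice in the protocol article. The Abstract (Objective) says: "Our hypothesis states that this kind of therapy can elicit equal or even better outcomes than conventional therapy". The Introduction (Aims and Hypothesis) expects satisfactory results "with similar or even better outcomes than those of conventional therapies".

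The size is set under Sample, Eligibility, and Allocation: "considering an effect size of 1.3, two tails, an error probability of .05, and a power of 0.8", "considering the global H4 histone acetylation levels variable from earlier studies". The same section gives the total ("We will recruit 24 participants, exclusively women aged 60 years and over") and the split ("stratified randomization for 2 groups with 12 participants each").

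Statistical Analysis names analysis of variance or Kruskal-Wallis, a gamma generalized estimating equation for the main outcomes, and correlations, with P<.05 as the only threshold. Neither that section nor the sample-size paragraph gives a non-inferiority or equivalence margin, or an interval criterion for calling the arms equal or similar.

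The Discussion expects both arms to improve and then says: "we expect the intervention group to show a significant improvement compared to the control group".

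**The concern.** Against an active comparator, equal or better is a non-inferiority claim. It needs a stated largest acceptable deficit and an interval that excludes anything worse. The sample size and the Discussion instead concern a difference between arms.

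With no margin, a significant result favouring the exergame fits *better*, and a non-significant one could be presented as fitting *equal*. Only a significant deficit would clearly count against the hypothesis. At stake is a claim that exergaming is as good as conventional kinesiotherapy, resting on limited precision rather than on evidence that the arms are close.

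**Working it through.** **Inputs.** From Sample, Eligibility, and Allocation: effect size d = 1.3, two-sided α = .05, power 0.8, 12 per arm. The effect size is read as a standardized mean difference, so results are in SD units; the article gives no underlying mean difference or SD. The margins and baseline correlations below are assumptions.

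**1. The stated sample size.**
- Normal approximation: n per arm = 2(1.96 + 0.842)²/1.3² = 15.70/1.69 = 9.3, so 10 per arm.
- Exact two-sided t-test (noncentral t, 2n − 2 df): 11 per arm gives power 0.826 and 12 per arm gives 0.861. The minimum is 11 per arm, or 22 in total.
- Dividing 11 by 3/π (the relative efficiency of the Wilcoxon-Mann-Whitney test under normality) gives 11.5, so 12 per arm, or 24 in total.

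The stated 24 therefore fits a two-sided difference test. No margin is needed to arrive at it.

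**2. Precision at 12 per arm, unadjusted end-of-treatment comparison.**
- 95% half-width = t(0.975, 22) × √(2/12) = 2.074 × 0.408 = 0.847 SD.
- If the observed difference is exactly 0, the interval runs from −0.85 to +0.85 SD.
- If the exergame arm is 0.84 SD worse, just short of significance, the interval reaches about −0.84 − 0.85 = −1.69 SD.

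**3. Precision with baseline adjustment.** The half-width becomes t(0.975, 21) × √(2/12) × √(1 − r²):
- r = 0.5: 2.080 × 0.408 × 0.866 = 0.74 SD.
- r = 0.7: 2.080 × 0.408 × 0.714 = 0.61 SD.

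**4. Chance of a significant two-sided test at 12 per arm (unadjusted, exact t).**

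| True difference (SD) | Power |
|---|---|
| 0.5 | 22% |
| 0.8 | 47% |
| 1.0 | 65% |
| 1.3 | 86% |

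Non-significance is more likely than not up to about 0.8 SD. Above that, significance becomes the likelier result.

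**5. What non-inferiority would need (true difference 0, 80% power, unadjusted).** Solving the noncentral t with 22 df for the margin at 12 per arm gives 1.05 SD at one-sided .05 and 1.20 SD at one-sided .025.

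For a chosen margin m at one-sided .025, n per arm = 2(1.96 + 0.842)²/m² = 15.70/m²; the exact t adds one per arm.

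| Assumed margin (SD) | n per arm | Power with 12 per arm |
|---|---|---|
| 0.3 | 175 | 10% |
| 0.5 | 63 | 22% |
| 0.8 | 25 | 47% |
| 1.0 | 16 | 65% |

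With baseline adjustment at r = 0.5 to 0.7, a 0.5 SD margin needs 48 to 33 per arm, still well above 12.

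**The case against.** The strongest reply is that the article never says a non-significant result will be taken as equality. Statistical Analysis contains no such rule, the Discussion's expectation is superiority, and the hypothesis speaks of what the therapy *can* elicit, which may be motivation rather than a formal test statement. This stands as a limit: a reader might infer that the trial would conclude equality from P>.05, but the text supports only that it could be presented that way.

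Two other strong readings fail.
- A reader might infer that 12 per arm makes non-significance likely whatever the truth. At the protocol's own 1.3 SD, power is 86%.
- A reader might infer that a null result excludes almost nothing. An observed difference of zero would exclude anything beyond about 0.85 SD, including the assumed 1.3 SD.

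The ±0.85 SD figure also rests on an unadjusted comparison, whereas Data Collection provides baseline values and the main analysis is a generalized estimating equation. Adjustment would narrow the interval, as shown, but would not make 12 per arm enough for a modest margin.

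The word superiority is not in the sample-size paragraph either. It is inferred from the two tails, the absence of a margin, the approximate reproduction of 24, and the Discussion.

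Finally, one might leave the margin to a full protocol or analysis plan. A margin determines the sample size, however, and this article fixes the size without one. A later document could name a margin, but it could not make 24 women enough for a modest one.

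**Conclusion.** The concern holds as a mismatch between the stated hypothesis and the design. The *equal* or *similar* half has no margin or interval rule, and the sample size was set for a difference of 1.3 SD in global H4 acetylation.

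On an unadjusted end-of-treatment comparison, 12 per arm leaves differences up to about 0.85 SD open even when the estimate is zero, and non-inferiority reaches 80% power only at a margin of about 1.05 to 1.20 SD. A margin of that size is close to the whole effect the trial assumes, so it can hardly mean similar. These figures rest on reading 1.3 as a standardized mean difference, on complete data from 12 women per arm and, for non-inferiority, on a true difference of zero. The sample size itself is adequate for the difference it assumes.

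**What to change.** - In the Abstract (Objective) and Aims and Hypothesis, restate the hypothesis as superiority of the exergame over conventional kinesiotherapy, tested two-sided, on global H4 acetylation. Outcome Measurements names several primary outcomes (epigenetic marks, balance, muscle strength), so the outcome must be named. Remove *equal* and *similar*.
- State in Statistical Analysis that P≥.05 is inconclusive and is not evidence of equality.
- Report the between-arm difference with its 95% confidence interval for every primary outcome.
- If *similar* is to stay, pre-specify and justify a margin for each outcome concerned, judge it against the confidence interval, and state that 12 per arm supports only margins of about 1 SD or more (unadjusted). A smaller margin means re-sizing.

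The first three changes are wording and reporting only; recruitment, conduct and data collection stay as they are. The sponsor gives up an equality claim that the trial could not have supported.

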**Methods:**

We will develop a virtual clinic exergame with 8 types of kinesiotherapy exercises. Afterward, we will conduct a 1:1 randomized clinical trial to compare the practice of kinesiotherapy with exergames (intervention group) against conventional kinesiotherapy (control group). A total of 24 older women will be enrolled for 1-hour sessions performed twice a week, for 6 weeks, totaling 12 sessions. We will assess outcomes using epigenetic blood tests, the Montreal Cognitive Assessment test, the Timed Up and Go test, muscle strength grading in a hydraulic dynamometer, and the Game Experience Questionnaire at various stages.

**Results:**

The project was funded in October 2019. Game development took place in 2020. Patient recruitment and a clinical trial are planned for 2021.

**Conclusions:**

Research on this topic is likely to significantly expand the understanding of kinesiotherapy and the impact of exergames. To the best of our knowledge, this may be one of the first studies exploring epigenetic outcomes of exergaming interventions.

**Trial Registration:**

Brazilian Clinical Trials Registry/Registro Brasileiro de Ensaios Clínicos (ReBEC) RBR-9tdrmw; https://ensaiosclinicos.gov.br/rg/RBR-9tdrmw.

**International Registered Report Identifier (IRRID):**

DERR1-10.2196/32729

## Introduction

### Background and Rationale

Human aging is a natural process that causes a series of neuropsychomotor changes, such as decreased muscle strength, proprioception, balance, and cognition [1,2]. An option to mitigate this deterioration is kinesiotherapy, a therapeutic exercise that trains body movements and postures in a planned and systemic way, improving the patient’s functional capacity, autonomy, and well-being [3].

Neuroprotective effects of physical exercise and the improvement of its clinical and functional outcomes are partly associated with the modulation of epigenetic marks, in both preclinical and clinical studies [4-9]. Epigenetics is the study of heritable changes in gene function that do not entail a change in DNA sequence [10]. Epigenetic marks are modulated by gender and time of the day [11]. Especially for older women, physical exercise has a role in improving health conditions [12-14], which is even indicated in biomarkers [15].

Older people face barriers to take part in exercise, but they identify positive aspects of strength and balance activities [16,17] and report positive perceptions about implementing technology to exercise [18]. Hence, appropriate programs and interventions based on education and training can help overcome the barriers [16]. Likewise, motivation and confidence for older persons can enable better performance in physical exercise [19]. In all these aspects, appropriate interactive technologies can have a facilitating role [20].

Virtual games are beneficial in physical therapy practice, particularly in the rehabilitation of functional balance, postural skills, and motor skills [21-23]. Exergames are virtual games that can capture the user’s real movements and promote physical activity, especially for older people [24]. This kind of game encourages the use of body movements to interact with the virtual scenario in a stimulating and integrative way, generating an enriched setting and greater motivation for progressing motor skills [25,26]. Game-based therapy can also be an alternative approach to improve cognitive functions, with improvements in different cognitive domains, such as executive function, visuospatial attention, verbal memory, and working memory [27]. Furthermore, rehabilitation exercises with exergaming have become an option for rehabilitation programs and have been adopted by physical therapists [28].

### Aims and Hypothesis

There is emerging evidence that physical exercise interventions can alter the epigenome, and the outcomes could be related to specific pathways [29,30]. However, to the best of our knowledge, there is still no evidence in the literature addressing the association of exergaming with epigenetic marks. Given the heterogeneity and complexity of the existing literature, more research is required in this emerging area to identify epigenetic marks that could serve as indicators of exercise adaptations [29]. In this perspective, this study aims to evaluate the effects of kinesiotherapy with exergaming on older women’s epigenetic marks and cognitive ability, alongside the evolvement of clinical functional variables. We hypothesize that this kind of therapy can elicit satisfactory results, with similar or even better outcomes than those of conventional therapies.

## Methods

This is an applied study with software development and analysis of its effects through a controlled, parallel, two-armed, open-label, randomized clinical trial. Figure 1 shows the procedure flowchart.

**Figure 1 figure1:**
[figure not shown]
Study procedure flowchart.

### Exergame Development

Exergames that require an individual to repeatedly reach for an object do not use the full potential of exergaming as a rehabilitation tool [31]. Taking this into account, we will develop an exergame with a virtual scenario based on a physiotherapy clinic. In this environment, 8 types of exercises practiced in kinesiotherapy sessions will be available, including squats, horizontal shoulder abduction, hip abduction, diagonal movement of the upper limb (Kabat diagonals), plantar flexion, elbow extension, elbow flexion, and horizontal shoulder adduction. Reference images from real environments will be used to model the setup and all interactable objects used by the avatars.

The clinic scenario will have windows that show an outdoor view with trees and clouds reacting to the wind. The lighting and animations will also change according to the day and time the user is playing, whether day or night. A male and a female character (avatar) will be available to play, selected according to the gender registered for each user. The objects that the avatar will interact with when performing an exercise will be automatically selected according to the type of exercise. Four camera positions will be implemented in the game. The game will have a menu with options for registration, settings, and types of exercise. During the execution of the exercises, information on the number of repetitions and completed series will appear on the screen, in addition to the execution time.

The exergame will be developed using the programming language C# (Microsoft Corporation), with the game engine Unity 3D (Unity Technologies). Both the scenario and the physiotherapy equipment will be modeled on Blender (Blender Foundation), open-source 3D creation software for animation, simulation, rendering, composition, and motion tracking. The characters will be created in Adobe Fuse (Mixamo), which also offers prebuilt animations and an autorigging tool in the mesh of the created characters. Some other tools, such as Audacity, for editing the sound effects, and Paint.NET (dotPDN LLC) for editing the interface sprites and object textures, may be used in the development of the game.

The participant plays the exergame by watching their avatar on a 42-inch monitor. The motion capture will use an Astra Pro depth sensor (Orbbec 3D Tech Intl Inc) and the software Nuitrack (3DiVi Inc), which analyzes the data obtained by the sensor to identify the user’s movements. To identify the completed repetitions and errors, the game will have rigidbody colliders in the avatar and in the scenario, passing the avatar positions to the scripts that evaluate whether the movement was correct or not.

One of the advantages of the proposed exergame over conventional therapy is that the game is more stimulating and has a joyful purpose, which provides a form of biomechanical biofeedback—feedback on measurements of movement, balance, postural control, and force output [32]. The exergame will have a dynamic virtual environment to engage participants, which will include elements such as background music, object sounds, avatars demonstrating movements as a form of instruction, sound and visual effects to reward achievements and exercise conclusions, scores, individual progress history, automatic counting of series and repetitions, the possibility of competition between participants, and control of times and turns. Hence, we expect to enhance the gains achieved during therapy, throughout the sessions, and perhaps even in a shorter period, as achieved by Henrique et al [21].

### Sample, Eligibility, and Allocation

We will recruit 24 participants, exclusively women aged 60 years and over, at the School Clinic of Studies and Professional Practices of the Regional Integrated University of Upper Uruguay and Missions, which is located in Erechim, Rio Grande do Sul, Brazil. The sample size was based on the studies that used a similar methodology to assess the effect of exercise on epigenetic marks and the effect of improved functional mobility induced by running in the older women, related to epigenetic marks [8,9], considering the global H4 histone acetylation levels variable from earlier studies [33,34]. Sample size was calculated using G*Power software [35] considering an effect size of 1.3, two tails, an error probability of .05, and a power of 0.8.

After the invitation to take part in the study, the participants will sign a consent form and complete a demographic questionnaire. The following inclusion criteria will be verified: age 60 years or older; ability to ambulate effectively; absence of any reported diagnosis of neurological, cardiac, or any other disease that restricts physical exercise; absence of depression confirmed by the Geriatric Depression Scale—Short Form [36]; cognitive ability confirmed by the Mini-Mental State Examination, Brazilian version [37]; and acceptance of the commitment not to undergo any other physical therapy during the study.

The sample will have stratified randomization for 2 groups with 12 participants each. Patients will be selected by order of agreement to participate in the study until the number of patients stipulated for either of the groups is reached. The intervention group will practice kinesiotherapy exercises with the exergame, whereas the control group will practice conventional kinesiotherapy exercises without exergaming. Owing to the nature of the intervention, masking of the physical therapists and participants is not possible. However, data will be collected and analyzed by professionals masked to the allocation of the groups.

### Outcome Measurements

Throughout the clinical trial, we will assess different data for two assays. The first assay will assess the acute and late effects on the participants’ epigenetic marks (primary outcome) as well as the cognitive ability (secondary outcome). Meanwhile, the second assay will assess the participants’ balance and muscle strength grading (primary outcomes), in addition to the postgame experience (secondary outcome).

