#### First Assay

Epigenetic marks will be assessed with blood tests. The samples will be collected by qualified and verified professionals, from veins located in the antecubital area, in a sanitized and cool place previously prepared for the procedure. Furthermore, 20 mL blood will be drawn using disposable syringes and needles. The venipuncture procedure will be applied and all national biosafety procedures will be followed. Initially, the blood will be divided into two tubes: a tube containing a separating gel that will receive 5 mL blood to obtain the serum. The other tube will contain the EDTA anticoagulant and will receive 15 mL blood. Then, Histopaque will be added in a 1:1 ratio to the tube with EDTA, which will then undergo a series of centrifuges for the extraction of plasma and peripheral blood mononuclear cells. The material will be stored in appropriate containers at −20 °C. Biomarker analysis will be performed using commercially available assay kits, according to the manufacturer’s guidelines.

The types of indicators that will be analyzed using biomarkers include plasma levels of the brain-derived neurotrophic factor (BDNF), a member of the neurotrophin family that has an important role in neuroplasticity and is associated with the process of memory and learning. We will also analyze the global acetylation levels of histones H3 and H4, which are epigenetic markers associated with increased transcriptional activity and gene expression. A previous study [9] identified that a single exercise session induced a state of global DNA hypomethylation but did not alter the global acetylation levels of H4 histone. However, these markers were not modified after more sessions, suggesting that epigenetic modulation in response to physical exercise is transient, which justifies an analysis comparing the acute and late effects.

Cognitive ability will be assessed using the Brazilian version of the Montreal Cognitive Assessment protocol [38]. This is a brief screening tool that assesses a wide range of cognitive functions, such as executive functions, visuospatial skills, memory recovery, digits, sentences, abstract reasoning, and orientation. The test time is estimated at 20 minutes and the maximum possible score is 30 points. The cutoff score is 26 points.

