### Statistical Analysis

Basic quantitative data will be determined by mean, SD, and median. Categorical data will be determined by simple frequency. Numeric data will be analyzed using statistical software SPSS, version 22 (IBM Corporation). The normality of the data will be tested using the Shapiro-Wilk test. Moreover, depending on the distribution, we will use one-way factor analysis of variance with Tukey post hoc (parametric data), or Kruskal-Wallis test (nonparametric data). To evaluate the main outcomes of the study, a generalized estimation equation with gamma distribution will be performed. To correlate the data, we will apply Spearman and Pearson analyses considering a 95% CI (*P*<.05). All analysis techniques can be adjusted or modified, if required, by the characteristics of the collected data.

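### Several co-equal primary outcomes, a sample size built on H4 acetylation alone at an unadjusted .05, and an analysis open to change: no single result carries a 5% error rate

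*Protocol article*

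**What the plan says.** **Primary outcomes.** Under Outcome Measurements, the first assay covers acute and late effects on "epigenetic marks (primary outcome) as well as the cognitive ability (secondary outcome"). The second covers "balance and muscle strength grading (primary outcomes), in addition to the postgame experience (secondary outcome").

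**Content of the epigenetic marks.** The First Assay section lists plasma BDNF among the indicators from the blood tests and adds: "We will also analyze the global acetylation levels of histones H3 and H4". It calls the two histone measures epigenetic markers and describes BDNF as a neurotrophin, so it is not certain that BDNF belongs to the primary outcome.

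**Times.** Under Data Collection, blood is taken at baseline, after the first session (acute) and after the whole intervention (late). Balance and strength are measured at baseline and at the end only.

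**Sample size.** Under Sample, Eligibility, and Allocation: "We will recruit 24 participants". The size was set "considering the global H4 histone acetylation levels variable from earlier studies", "considering an effect size of 1.3", with "two tails, an error probability of .05, and a power of 0.8".

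**Analysis.** The Statistical Analysis section assigns the main outcomes to a generalized estimating equation (GEE) with a gamma distribution, and gives no significance level or contrast in that sentence. It attaches P<.05 to the Spearman and Pearson correlations. It ends: "All analysis techniques can be adjusted or modified, if required, by the characteristics of the collected data".

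**The concern.** Choosing the primary outcome is a protocol decision, and here it is left open. Three blood markers (or two, if BDNF is not counted) at two times stand beside balance and strength, with none placed first. The one variable that the sample size is built on has no special standing among them.

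A reader of the results could therefore be shown whichever primary result reached significance, and could not treat it as a claim with a 5% error rate. The acute-or-late question matters in particular because the First Assay section itself describes epigenetic responses to exercise as transient. The authors thus expect the two times may differ, but do not say which one decides.

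The closing sentence of the Statistical Analysis section adds a second opening. It sets no limit on when a change may be made and does not require a change to be reported as such.

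**Working it through.** **Inputs.** From Sample, Eligibility, and Allocation: effect size 1.3 (read as a standardized difference between two means), two-sided alpha 0.05, power 0.80, 12 per arm. From Outcome Measurements, First Assay and Data Collection: the outcomes and times listed above. My assumptions: each primary is tested at .05, all null hypotheses are true, and any one significant result counts as success.

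**1. The plan's own figure.** For a two-sample t test with n per arm, the noncentrality is d × √(n/2) on 2n − 2 degrees of freedom.
- n = 11: 1.3 × √5.5 = 3.05; power 0.826
- n = 12: 1.3 × √6 = 3.18; power 0.861

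The smallest size reaching 0.80 is 11 per arm (22 in total). The stated 24 is two more and is consistent with the stated inputs. It is a size for one comparison of one variable at .05.

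**2. How many primary tests.**
- Three markers × two times + balance + strength = 3 × 2 + 2 = 8
- Without BDNF: 2 × 2 + 2 = 6
- One group-by-time test per outcome from the GEE: 3 + 1 + 1 = 5
- The same without BDNF: 2 + 1 + 1 = 4

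The article does not settle which applies.

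**3. Chance of at least one false positive.** For k independent tests this is 1 − 0.95^k. The other columns assume normal test statistics with a common correlation.

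| Tests | Independent | Correlation 0.5 | Correlation 0.7 |
|---|---|---|---|
| 8 | 33.7% | 25.0% | 19.1% |
| 6 | 26.5% | 20.7% | 16.4% |
| 5 | 22.6% | 18.3% | 14.8% |
| 4 | 18.5% | 15.6% | 13.0% |

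If, among eight tests, only the two times of the same marker are correlated, the figure stays at 33.1%, 32.2% and 30.5% for correlations of 0.3, 0.5 and 0.7. If each assay is treated as its own family, the figures are 1 − 0.95^6 = 26.5% and 1 − 0.95^2 = 9.8%.

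**4. What the remedies cost in power** (12 per arm, d = 1.3).
- One primary at .05: 0.86
- One of two primaries at .05/2 = .025: 0.78
- Bonferroni over eight, .05/8 = .00625: 0.57; reaching 0.80 would take 18 per arm (36 in total)

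Naming one primary is therefore far cheaper than dividing alpha over all of them.

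**The case against.** **The count and the level are not in the text.** A reader might infer that there are at least eight primary tests, each judged at P<.05, and so a one-in-three chance of a false success. The article does not support this as fact. P<.05 is written for the correlations; the only other .05 is in the sample size calculation. A GEE may give one test per outcome, hence four or five. The one-in-three figure also needs independence and a rule that any one result suffices, and no such rule is stated. This objection stands, and it is why the size is given as a range. The count could also exceed eight, since the article does not list the muscle groups tested for strength.

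**Multiplicity detail may sit in a document not shown.** This is fair, and the absence of an adjustment method is not the point here. What remains is stated text: several outcomes designated as primary, a sample size tied to one of them, and an open licence to modify.

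**The licence may be meant as a distributional fallback, and the analysts are masked.** The sentence follows a plan to choose tests by normality, and the allocation section says that masked professionals collect and analyse the data. Masking limits the scope for choosing an analysis by its between-arm result. It does not rank the primaries, and the sentence does not confine changes to the masked stage. A reader might infer that this flexibility pushes the error rate beyond the figures above. It may, but the article gives no basis for a number, and none is included.

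**The late H4 contrast is not dictated by the article.** This is correct. The sample size names H4 acetylation but no time point. The First Assay section also cites a study in which one session left H4 acetylation unaltered and more sessions did not modify the markers. The authors must choose the time and confirm that 1.3 applies to it.

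**Conclusion.** The concern holds in a limited form. The protocol names several co-equal primaries, sizes the trial on H4 acetylation alone at an unadjusted two-sided .05, gives H4 no priority, and allows all techniques to change with the data. If each primary were tested at .05 and any one counted as success, the chance of at least one false positive would be about 13% to 34% under a global null. The lower end is four tests at correlation 0.7, and the upper end is eight independent tests. Every count and correlation in the table is more than twice the nominal 5%. Confidence is high that no primary has priority, and lower for any single figure, because the count, level and success rule are inferences. This should be corrected before the data are analysed.

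**What to change.** 1. Name one primary: the between-arm difference in global H4 acetylation at one pre-specified time, two-sided .05. After the complete intervention is one candidate, for the authors to confirm. Power is about 0.86 with 12 per arm if the effect size of 1.3 holds for that contrast.
2. Make the other H4 time point, H3, BDNF, Timed Up and Go and muscle strength secondary, with Holm adjustment or labelled exploratory.
3. Replace the last sentence of the Statistical Analysis section with, for example: *Analyses are fixed before the masked analysts are unmasked, and any later change is reported as post hoc.*
4. If each assay must keep a primary, name one in each and test both at .025. The resulting power of 0.78 at 1.3 applies to H4 only, because the article gives no effect size for balance or strength.

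The cost is wording, with no added participants. The downside is that balance and strength become secondary claims.
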